**Figure 5 figure5:**
[figure not shown]
Structure of the data acquisition system.

The smartphone also generates text files containing time stamps that indicate the start and end of each exercise performed. As the exercises are tracked using 2 different apps, 2 separate label files are generated each day: one corresponding to the 8 exercises of the Monipar sequence and the other to the specific free-living activity. These text files are stored on the smartphone until the end of the study.

Upon completion of the study and the return of the devices by the participants, the collected data are extracted. The extraction process differs based on the type of wearable device, though in both cases, it requires the use of a computer. For the smartphone, text files containing the temporary labels are extracted via a direct cable connection to the computer. Conversely, for the smartwatch, the compressed data files from the inertial sensors are retrieved over a Wi-Fi connection, ensuring that both the watch and the computer are connected to the same network.

### Data Analysis

The resulting database from the data collection campaign will comprise signals from the 3 axes of the smartwatch’s accelerometer and gyroscope. These data will be divided into 3 distinct parts. First, it will include the evaluation of the sequence of 8 Monipar exercises, conducted both in supervised and labeled conditions following the MDS-UPDRS III scale, as well as in unsupervised free-living conditions. Second, it will encompass the performance of the specific free-living exercise, 1 minute of beating eggs, performed under supervised conditions at the association and under unsupervised free-living conditions. Finally, the database will contain the daily recording of 4 hours of free-living activity, accompanied by the physical activities performed during the day and participant-completed notebooks detailing activities such as eating, resting, and taking medication.

A comprehensive data analysis will be proposed to identify appropriate indicators and validate their effectiveness. Various scenarios will be proposed based on the collected data, providing insights into the potential applicability of these biomarkers in diverse clinical and therapeutic contexts.

A set of biomarkers will be defined for the identification of patients with PD by comparing their data with those of healthy participants. Another collection of biomarkers will be calculated to predict MDS-UPDRS scores in patients with PD using the labeled sessions, enabling a more detailed understanding of the relationship between the recorded signals and clinical evaluations.

In addition, a comparative analysis will be undertaken using the previous or new biomarkers between measurements collected in supervised clinical contexts and those recorded in unsupervised, free-living conditions. Similarly, the validity and performance of the proposed biomarkers will be examined across different age groups, given the motor variability present among various age ranges. This will help determine the consistency and reliability of the data across different contexts. Furthermore, the study will explore the correlation between the specific free-living exercise, which is strongly linked to bradykinesia, and the MDS-UPDRS exercises of the Monipar sequence. This correlation will be examined for both data collected at the APM and at the participants’ homes, providing insights into how specific activities reflect the motor symptoms in patients with PD across diverse settings.

To define these potential biomarkers, data analysis methods are developed and organized according to a data analysis workflow. As the entire database is based on the triaxial accelerometer and gyroscope signal, the pipeline will be applied to the whole database. Figure 6 shows the proposed pipeline. All data analysis will be conducted using Python (Python Software Foundation) and MATLAB (MathWorks).

**Figure 6 figure6:**
[figure not shown]
Data analysis pipeline.

First, the correct recording and collection of the expected data for each participant will be verified to ensure that all records are properly saved and stored. Once confirmed, the data will be labeled by combining the signals collected from the smartwatch with the activity tags generated by the smartphone. The 8 exercises of the Monipar sequence and the forced free-living activity will be tagged, with automatic tagging enabled by the synchronization between the 2 devices. However, a manual check will be conducted to ensure the accuracy of the start and end times for each tagged activity.

An individual analysis will be conducted for each participant’s data collected in unsupervised, free-living conditions to assess the reliability and trustworthiness of the signals. Although all participants will receive the same clear and standardized instructions, this step helps ensure that variations in guidance do not impact performance. To achieve this, the signals recorded in a supervised setting—reviewed by at least 4 experts (including a physiotherapist specialized in MDS-UPDRS and 3 other researchers or engineers to ensure correct exercise performance)—will be used as a reference for comparison with those recorded during free-living conditions. This will be done both for the set of exercises of the Monipar sequence and for the forced free-living activity.

Participants with corrupted, incomplete, or inaccurate data will be considered for inclusion only if they possess a complete supervised recording and at least half of the expected unsupervised data, ensuring sufficient data quality for reliable analysis.

The sessions conducted at the beginning and end of the study for the PD group will also be labeled, as these recordings are accompanied by evaluations performed using the MDS-UPDRS by a physiotherapist specialized in PD. It is crucial to highlight that the initial and final MDS-UPDRS assessments are performed by the same evaluator, who will evaluate each of the MDS-UPDRS exercises performed. This introduces 2 sources of subjectivity: one related to the evaluator’s individual judgment and the other inherent to the interpretation and use of the MDS-UPDRS scale, which is subjective by nature. To mitigate this potential bias, the evaluator had undergone standardized training procedures before assessments, and intrarater reliability will be monitored throughout the study to ensure consistency in scoring. These scores serve as the reference label for assessing the participant’s current condition and can be used to categorize individuals into groups based on the intensity of motor symptoms.

Once the data have been labeled, a preprocessing step will take place. During this phase, various actions will be performed depending on the specific analysis objectives. These actions include combining the 3 signals from each sensor using the Euclidean norm; applying filters (eg, low-pass, high-pass, or band-pass) to isolate specific frequency ranges; segmenting the signal into windows with or without overlap; resampling the signal to a different frequency; or transforming the time-domain signal into the frequency domain, for example. These preprocessing steps aim to prepare the data for further analysis, ensuring that the signals are in the optimal format for extracting meaningful insights.

Following the preprocessing phase, feature extraction will be conducted to identify and compile characteristics from the processed signals for further analysis. This process transforms raw data into a structured set of measurable attributes or features, facilitating analysis or modeling. The goal of this step is to reduce data complexity while preserving its most relevant and informative aspects. Extracted features may encompass statistical properties of the signals, such as mean, SD, or range, in both time and frequency domains [49]. In addition, they may be derived from mathematical computations or based on biomechanical analyses of the movements performed, targeting specific motor symptoms, including resting tremors, bradykinesia, or gait abnormalities.

Depending on the amount of extracted features, it may be beneficial to reduce their number, as a manageable and well-defined set of characteristics is essential for establishing reliable biomarkers.

Statistical and probabilistic analyses will be performed using the proposed features to identify potential biomarkers that correlate with the various PD symptoms being studied. These biomarkers may be consistent across all symptoms or distinct for each symptom, as well as for different activities.

Furthermore, artificial intelligence classification models will be developed using the proposed features. Given the medical context of this study case, it is crucial that the models are interpretable and explainable. To achieve this, machine learning algorithms such as random forests or decision trees will be used, as these models can be subjected to explainable artificial intelligence techniques. In addition, deep learning models will be incorporated to enhance the predictions made by the machine learning models. The most relevant features will be extracted from the models to identify digital biomarkers for motor symptoms of PD.

The evaluation of the classification models will be assessed through a confusion matrix, alongside metrics such as sensitivity, specificity, or accuracy. Other performance measures, such as the area under the receiver operating characteristic curve, could be considered to offer a more thorough evaluation of the model’s effectiveness.

In unsupervised measurements conducted at participants’ homes, the MDS-UPDRS score determined in the clinical setting can be used as a benchmark to evaluate its alignment with the results obtained from these unsupervised measurements. However, considering the intrinsic subjective nature of MDS-UPDRS labeling, unsupervised learning methods, such as association rules or clustering algorithms, will also be explored to analyze the assessment of the exercises performed to uncover data-driven patterns. This approach aims to provide a complementary perspective and reduce reliance on subjective evaluations.

In addition, the 4-hour period of free-living activity, recorded alongside the patient’s self-reported medication intake times, will be analyzed to assess the relationship between medication administration and the patient’s condition during the period of inertial signal recording. This analysis will involve segmenting the free-living activity data into periods before and after medication intake and comparing the evolution of the inertial signal and defined biomarkers during these periods.

All relevant features, both before and after model training, will be examined and used to define the biomarkers. These biomarkers will serve several purposes: differentiating patients with PD from healthy participants, assessing the MDS-UPDRS stage in both supervised and free-living conditions, and evaluating the ability of free-living activities to correlate with the disease stage of each patient. In addition, these biomarkers will help elucidate the relationship between the MDS-UPDRS assessment and free-living motor activities and assess the impact of surgical and therapeutic treatments and interventions on motor performance.

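### The supervised signals serve both as the test of whether home recordings can be trusted and as the comparator in the supervised-versus-home analysis, and the plan does not keep the two uses apart

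*Protocol article*

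**What the plan says.** All the relevant text is in the protocol article, Methods, Data Analysis.

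**The check.** After Figure 6, the article plans an individual analysis of each participant's unsupervised data "to assess the reliability and trustworthiness of the signals". The yardstick is the set of supervised signals, reviewed by at least four experts, which "will be used as a reference for comparison with those recorded during free-living conditions". The stated aim is that "this step helps ensure that variations in guidance do not impact performance". On scope: "This will be done both for the set of exercises of the Monipar sequence and for the forced free-living activity".

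**The inclusion rule.** The next paragraph reads: "Participants with corrupted, incomplete, or inaccurate data will be considered for inclusion only if they possess a complete supervised recording". It also requires "at least half of the expected unsupervised data, ensuring sufficient data quality for reliable analysis".

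**The later analysis.** Earlier in the section, a comparative analysis of biomarkers is planned "between measurements collected in supervised clinical contexts and those recorded in unsupervised, free-living conditions". Of the planned comparisons the article says: "This will help determine the consistency and reliability of the data across different contexts".

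The article gives no similarity measure, no cut-off and no definition of inaccurate. It does not say whether the supervised-versus-home comparison will use every technically sound home recording whatever the check finds.

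**The concern.** Home data should be screened by something other than the quantity they will later be compared with. Here the supervised signal decides whether a home signal can be trusted, and it is also one side of the comparison from which consistency is inferred. The tasks are the same in both uses.

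A home session can differ from the clinic session for two reasons. The task may have been done wrongly, or the participant may really move differently at home. The second is what the study sets out to observe: the Introduction (BioClite Project) presents direct comparison of clinical and real-world data as an advance over earlier work. A check based on resemblance to the clinic signal cannot tell the two reasons apart.

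If dissimilar sessions are dropped, high agreement may partly reflect selection, and a true setting effect looks smaller than it is.

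**Working it through.** The article states no agreement figure, similarity threshold, power or alpha that bears on this, so there is nothing to reproduce. The check has two parts.

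**1. The link in the text**

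| Step | Yardstick or comparator | Data | Stated consequence |
|---|---|---|---|
| Trustworthiness check | Supervised signals | Home Monipar and egg beating | None stated |
| Inclusion rule | Complete supervised recording and at least half of the expected home data | Participants with corrupted, incomplete or inaccurate data | Conditional inclusion |
| Comparative analysis | Supervised measurements | Home measurements (biomarkers) | Read as consistency and reliability |

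File completeness has its own verification step, and the manual check concerns start and end times. The comparison with supervised signals is the only described step that judges how a home task was performed. It is therefore a likely source of the label inaccurate, but the article does not say so.

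Counted in daily sessions, half of 7 is 3.5, so a retained participant needs at least 4 of 7 and can lose at most 3/7 = 43%.

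**2. Size, if dissimilar sessions are removed**

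From the article: 20 participants per group (40 in all), 7 home days, at least half of the home data.

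Assumed: a unit-variance biomarker; true single-session correlation ρ; share of sessions removed q; correlation k between the screening measure and the biomarker difference. Each participant is screened against his or her own supervised recording.

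Model: supervised value S = t + e and home value Hj = t + ej, with Var(t) = ρ and Var(e) = Var(ej) = 1 − ρ. The difference D = Hj − S has SD √(2(1 − ρ)), which is 1 for ρ = 0.5. Sessions with the largest absolute screening value are removed, and participants with fewer than 4 of 7 sessions left are dropped.

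*The screen is the biomarker difference itself (k = 1), 20 participants:*

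| True value | q = 0 | 10% | 20% | 30% |
|---|---|---|---|---|
| ρ = 0.3, observed correlation | 0.29 | 0.48 | 0.59 | 0.67 |
| ρ = 0.5, observed correlation | 0.48 | 0.64 | 0.72 | 0.79 |
| ρ = 0.7, observed correlation | 0.68 | 0.78 | 0.84 | 0.88 |
| Shift of 0.5 SD (ρ = 0.5), observed shift | 0.50 | 0.34 | 0.23 | 0.15 |

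*The screen is only partly related to the biomarker difference (ρ = 0.5, 40 participants):*

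| k | 10% removed | 25% removed |
|---|---|---|
| 1 | 0.64 | 0.76 |
| 0.7 | 0.56 | 0.61 |
| 0.5 | 0.53 | 0.55 |
| 0.3 | 0.50 | 0.51 |
| 0 | 0.49 | 0.49 |

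With nothing removed, the observed value is already slightly below 0.5, so the k = 0 row means no inflation.

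*The opposite case.* If the 10% removed are wrongly performed sessions that carry only noise, removal moves the correlation from 0.44 to 0.49, towards the truth.

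**The case against.** The strongest reply is that the article describes an assessment and no rejection rule. Its only explicit inclusion rule works at participant level and is mainly about completeness. Inaccurate could as well mean mis-tagged times or a wrongly executed exercise, and confirming that a tagged segment shows the instructed task is ordinary quality control. The check also looks at signals, whereas the later comparison uses biomarkers extracted after preprocessing. The study calls itself exploratory and plans no confirmatory test of agreement.

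Most of this stands, and it limits the claim. A reader might infer that home recordings are accepted or rejected by closeness to the supervised ones, so that agreement is inflated by construction. The text does not support that: it states no metric, cut-off or session-level rule, and the tables show that inflation fades as the screen becomes less related to the biomarker. The direction is not certain either, because removing truly wrong executions can correct the estimate. A reader might also take the loss of half of all home data as the case to plan for. Counted in sessions, a retained participant cannot lose that much.

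Whether the checkers know the participant's group is not stated. A condensed article can leave that to the analysis plan, so it forms no part of this point.

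The reply does not remove the double use. The article itself names the supervised signal as the reference for trust and then uses supervised measurements as the comparator, with nothing to separate the two.

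**Conclusion.** The point holds in conditional form. If a poor match to the supervised signal leads to removal of home Monipar or egg-beating recordings, supervised-versus-home agreement is biased upward and real setting differences shrink. For a true correlation of 0.5 with 10% of sessions removed, the observed value is about 0.53 to 0.64 when the screen correlates 0.5 to 1 with the biomarker difference. It stays at about 0.49 when they are unrelated. If nothing is removed, there is no bias from this source.

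These sizes rest on assumed values of the correlation, the share removed and the link between screen and biomarker. None of them is in the article. The rest of the 4-hour daily record is not screened in this way by the text and is unaffected. This is an inexpensive correction to make before any data are excluded. It is not a flaw that invalidates the study.

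**What to change.** For the supervised-versus-home comparison:

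- Define inaccurate home data only by criteria that do not use similarity to the supervised signal: file intact, watch worn, sampling present, start and end tags present, minimum duration, instructed task recognisable.
- Report agreement on all home recordings that meet these criteria, with the number removed by group.
- Show results on any similarity-screened set only as a sensitivity analysis, labelled as such.

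The cost is a change of wording in the analysis plan and a small change to the quality-check script. Reported agreement may be somewhat lower. Some wrongly performed home sessions may stay in the main set and add noise; the sensitivity analysis would show how much that matters.

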**Results:**

Participant recruitment and data collection started in December 2024 and will continue until spring 2025. The study aims to enroll 20 participants with PD and 20 healthy controls.

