### Study Design

This study comprises 1 week of free-living monitoring of 20 participants with PD and 20 healthy control participants. The proposed number of participants in this study is comparable to those found in the literature for defining biomarkers in PD (mean 15, SD 6.8 patients with PD) [28,31,36-39] or for monitoring PD motor symptoms (mean 15.4, SD 4.5 patients with PD) [29,40-45]. Small samples are common in exploratory research with wearable sensors, particularly in populations considered vulnerable and hard to recruit such as individuals with PD. Such studies are important for early validation of methods and identifying key trends to inform future research. While the sample size limits detailed subgroup analyses, it is adequate for assessing general patterns and methodological feasibility. All participants will undergo the same experimental protocol, which includes the following:

A baseline assessment to establish initial measuresA 1-week period of unsupervised free-living activity monitoring to capture naturalistic dataA final evaluation to reassess clinically and compare with baseline results

The study schema is illustrated in Figure 1, providing an overview of the structured protocol and its key phases.

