Although previous studies have highlighted a lack of consensus among patients regarding data ownership and access, suggesting shortcomings in the communication and understanding of informed consent procedures [52], in this study, all participants will be thoroughly informed about the study details before their participation begins. Written informed consent will be obtained from each participant in accordance with Good Clinical Practice guidelines and International Conference on Harmonization standards. Furthermore, each participant will be provided with a copy of the signed consent form to allow them to review the terms at any time, thereby reinforcing transparency and autonomy in the data collection process.

Participation in this study is completely voluntary. Participants can withdraw at any time without providing a reason, and their decision will not affect the quality of care or services they receive from the organization. Upon withdrawal, any data previously collected from the individual will be excluded from the analysis, and no replacement participants will be recruited.

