## Discussion

### Anticipated Findings

This paper presents the research protocol for the BioClite project at APM, a study focused on monitoring PD using smartphones and smartwatch sensors. The study aims to compile a dataset comprising 20 participants with PD and 20 healthy controls for assessing motor symptoms in individuals diagnosed with PD. The ultimate goal of the study is to facilitate the definition of digital biomarkers for assessing motor symptoms in patients with PD.

In recent years, the use of technologies such as smartphones [53], smartwatches [46], and other wearable sensors [32,54] for monitoring PD has garnered increasing attention. Furthermore, advancements in computational capabilities have enabled the development of algorithms capable of recognizing complex movements and patterns [25]. These developments highlight the considerable potential of portable solutions to effectively monitor PD and provide valuable insights into its progression and management.

The high variability in motor symptoms associated with PD necessitates the evolution toward continuous patient monitoring. In consequence, the BioClite study aims to bridge this gap by transitioning from controlled clinical assessments to follow-up in nonsupervised free-living environments, as high variability in motor symptoms associated with PD necessitates the evolution toward continuous patient monitoring.

This approach involves evaluating participants through the MDS-UPDRS exercise sequence and the specific free-living activity of beating eggs by analyzing accelerometer and gyroscope signals from a commercial smartwatch. These activities are performed in both supervised clinical settings and unsupervised free-living conditions. Although the inclusion of structured tasks introduces a semisupervised element, it achieves a necessary balance between methodological standardization and validity for initiating the transition to free-living contexts. This dual approach ensures a comprehensive assessment of motor symptoms under controlled conditions and in participants’ daily lives.

The proposed biomarkers will be designed for app in both supervised clinical context and unsupervised free-living environments, enabling neurologists and PD specialists to evaluate symptoms and monitor their progression across both contexts.

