### Limitations

Despite its potential, the study has several limitations. The data collection period is limited to a week, which may not fully capture the long-term variability of symptoms in PD. In addition, the inclusion of unsupervised data introduces potential biases. Although efforts are made to standardize data collection (eg, tagging activities and monitoring data quality), variations in how participants perform tasks in a free-living environment cannot be fully controlled. Advanced signal processing techniques and robust filtering methods will be explored to mitigate these effects.

Another challenge relates to participant adherence. Not all participants may complete the entire protocol or provide the expected volume and quality of data. Variations in motivation, cognitive impairment, or practical barriers (eg, technical issues) could reduce the completeness of the dataset. Personalized follow-up and automated reminders will be used to improve adherence.

Future research will focus on exploring the use of this technology in long-term study periods to assess the potential use of the defined digital biomarkers for continuous and free-living monitoring between clinical visits. Moreover, the approach developed here can be adapted for use in clinical trials and therapeutic monitoring. Integration into digital health platforms may support large-scale longitudinal studies and personalized medicine approaches in PD.

Both the anonymized dataset and the results of the study will be made publicly available, supporting transparency, reproducibility, and further research in the field of PD digital health.

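### The single completeness rule for participants with incomplete data has no exception by analysis, so read literally it removes people from supervised-only analyses for want of home data

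*Protocol article*

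**What the plan says.** The protocol article, Methods, Data Analysis (text after Figure 6), sets one rule for people whose data are defective or partly missing. They are "considered for inclusion only if they possess a complete supervised recording and at least half of the expected unsupervised data". The two conditions are joined, the unit is the participant, and no analysis is exempted.

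The same section plans analyses with different data needs. MDS-UPDRS scores are to be predicted from the labeled sessions, which are the two supervised visits. The correlation of egg beating with the Monipar exercises is to be examined separately for association data and home data. The 4-hour free-living recording is to be compared before and after medication intake.

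On withdrawal, Ethical Considerations states: "Upon withdrawal, any data previously collected from the individual will be excluded from the analysis, and no replacement participants will be recruited".

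On expected incompleteness, Limitations states: "Not all participants may complete the entire protocol or provide the expected volume and quality of data". It adds: "Variations in motivation, cognitive impairment, or practical barriers (eg, technical issues) could reduce the completeness of the dataset".

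On numbers, the abstract's Results paragraph states: "The study aims to enroll 20 participants with PD and 20 healthy controls". Anticipated Findings uses the same figure for the dataset: "The study aims to compile a dataset comprising 20 participants with PD and 20 healthy controls". No allowance for loss is given.

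**The concern.** A completeness rule should ask whether a person has the data that a given analysis needs. This one asks whether the person has the data that all analyses together need. A participant with PD who has two complete, scored visits but 3 of 7 home days lacks nothing for the supervised analyses, yet fails the rule.

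Two things are at stake. First, with 20 per group, each needless exclusion costs 5% of a group (1/20). Second, entry to the supervised analyses comes to depend on adherence at home, which the article itself links to motivation and cognitive impairment. Results meant to describe performance at a supervised visit would then rest on people selected for what they did during the following week.

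**Working it through.** **1. Data needed against data required.** Each planned analysis is set beside the joint rule.

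- *MDS-UPDRS prediction from labeled sessions:* needs supervised recordings and scores. The rule also demands half of the home data. That demand serves no purpose here.
- *Egg beating against Monipar, association data:* needs supervised recordings only. The mismatch is the same.
- *Home Monipar and home egg beating:* the article uses the supervised signals as the reference for judging the home signals, and the clinic score as a benchmark. Requiring both kinds of data is justified.
- *4-hour recording before and after medication:* needs home data and intake times. The supervised reference plays no stated part, so the demand for a complete supervised recording is not explained.

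**2. The plan's own figure.** The 20 + 20 has no significance level, power or effect size behind it, so no sample-size formula can be reproduced. It is supported as "comparable to those found in the literature for defining biomarkers in PD (mean 15, SD 6.8 patients with PD", with a second literature mean of 15.4. Twenty lies above both. No loss rate is stated, so every rate below is an assumption.

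**3. People lost from supervised analyses.** Let w be the proportion withdrawing, s the proportion failing the supervised condition and u the proportion failing the home condition, taken as independent. Then, per group:

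- joint rule: 20(1−w)(1−s)(1−u)
- rule per analysis: 20(1−w)(1−s)

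| w, s, u | Joint rule | Per analysis | Difference |
|---|---|---|---|
| 5%, 5%, 5% | 17.1 | 18.1 | 0.9 |
| 5%, 5%, 10% | 16.2 | 18.1 | 1.8 |
| 10%, 5%, 10% | 15.4 | 17.1 | 1.7 |
| 10%, 10%, 15% | 13.8 | 16.2 | 2.4 |

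Differences are taken before rounding. In the last row the joint rule falls below both literature means (15 and 15.4), while the rule per analysis stays above them.

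**4. Who is removed.** The article does not say whether half counts days, hours or exercises. Suppose it means at least 4 of 7 days, with independent days and a constant daily adherence a. The chance of passing is P(X ≥ 4), X ~ Binomial(7, a): 0.997 at a = 0.9, 0.967 at 0.8, 0.874 at 0.7 and 0.710 at 0.6. The threshold is mild for good adherers and falls mainly on poor ones.

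**5. Effect on precision.** For an assumed sensitivity of 0.85, the approximate 95% half-width is 1.96√(0.85 × 0.15/n): 0.156 at n = 20, 0.165 at 18, 0.175 at 16 and 0.187 at 14. The loss is real but modest.

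**6. Enrolled against analysed.** With per-person loss q from any cause and no replacement, the expected number is 20(1−q) per group and the chance that all 40 remain is (1−q)^40.

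| q | Expected per group | P(all 40 remain) |
|---|---|---|
| 2% | 19.6 | 0.446 |
| 5% | 19 | 0.129 |
| 10% | 18 | 0.0148 |
| 20% | 16 | 0.00013 |

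**The case against.** The strongest reply has five parts.

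- **The supervised requirement has a purpose.** Supervised signals are the stated reference for the home exercises. This stands, and the fix keeps the requirement there. It does not explain the home-data condition for supervised analyses.
- **The rule leaves discretion.** People are to be considered for inclusion, which sets a minimum and does not make the decision. This stands in part: the discretion applies only to those who meet both conditions, so it cannot rescue someone with too little home data.
- **Analysis sets belong in an analysis plan that is not shown.** That is true of the detail. The article has nevertheless stated a rule at participant level, and that rule does not fit its own planned analyses.
- **Mitigation exists.** Technical Support promises an analysis of each person's adherence, and Limitations names follow-up and reminders. These help, but they are not a comparison of excluded with retained participants.
- **The study is exploratory and makes no power claim.** This stands and limits the weight of the point.

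A reader might infer three stronger claims that the documents do not support:

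- *The design cannot deliver 20 + 20.* The figure is worded as an aim, and it is reached if nobody is lost.
- *Withdrawn participants' data are erased.* The text says they are excluded from analysis, within the terms of voluntary participation.
- *The analysed PD group will be fitter than the controls.* Limitations speaks of participants generally. Both groups must function independently, and the PD group is limited to Hoehn and Yahr 2.5 or below. The personalized follow-up described for the PD group could raise its retention. Bias that differs by group is possible, but neither its existence nor its direction can be derived.

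**Conclusion.** The point holds in a limited form. Followed as written, the rule removes people from supervised-only analyses for lack of data that those analyses do not use. It also makes entry to those analyses depend on home adherence. The avoidable loss is about 0.9 to 2.4 people per group, given the assumed rates and independence in the working. The documents give no rates, so this range is illustrative. The effect on precision is modest, no stated power is broken, and at 5 to 10% overall loss the expected 18 to 19 per group still exceed the literature means cited. The size and direction of any selection bias remain unknown.

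A smaller point also stands. With no replacement, any loss leaves fewer than 40 to analyse, so 20 + 20 describes enrolment and should not be read as the number analysed. The withdrawal term itself is not an error.

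**What to change.** Replace the single rule with completeness per analysis:

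- Supervised analyses use everyone with a valid supervised recording of the task concerned.
- Home Monipar and egg-beating analyses require the supervised reference recording and the half-data minimum.
- Analyses of the 4-hour recording that do not use the supervised reference, such as the comparison before and after medication, require only the home-data minimum.

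Say what half counts (days, hours or exercises) and whether one or both supervised visits must be complete. Report excluded against retained participants by group, and repeat the home analyses without the half-data threshold as a sensitivity analysis. Describe 20 + 20 as the number enrolled, and give the number analysed for each analysis.

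The cost is wording, best settled before analysis starts, plus a short table. No new data and no change to the consent form are needed. The drawback is that the number analysed will differ between analyses, so comparisons across them must state which participants each one includes.
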